## Abstract

**Background:**

Despite effective strategies to prevent substance use and substance use disorders among college students, challenges remain. As young adults’ preference for and comfortability with web-based technology continues to increase, leveraging innovative approaches to rapidly evolving mHealth technology is critical for the success of lowering the risk for substance use and related consequences in college populations, and especially those at Hispanic Serving Institutions. Therefore, the present study describes the rationale, development, and design of iSTART, a novel web-app to prevent substance use among students.

**Methods:**

The web-app was developed following the intervention mapping protocol, and in collaboration with numerous stakeholders, including a community-based partner specializing in substance abuse prevention and treatment. A 30-day multi-module web-app intervention was developed based on key theoretical constructs, behavior change strategies, and practical module components: attitudes (knowledge), perceived susceptibility (risk perceptions), subjective norms (normative re-education), and self-efficacy (refusal skills). This intervention will be evaluated via a time series design using a sample of 600 students randomly assigned to either the intervention, comparison, or control condition at a public institution in southern California.

**Discussion:**

The iSTART web-app is an innovative and sustainable program ideal for college campuses with diverse student populations. If this prevention web-app is successful, it will significantly contribute to the evidence of effective substance use interventions in the college setting, and identify the benefits of mHealth programs to prevent future substance use.

**Trial registration:**

NCT05362357 retrospectively registered on May 4, 2022 on clinicaltrials.gov.

## Background

Although the college years are a period of exploration and positive transformation, college students are at high risk for health-compromising behaviors such as alcohol and drug use. In 2020, approximately one-third of U.S. college students reported past-month binge drinking, 43% used marijuana, 16% used nicotine vaping devices, and 3% misused prescription drugs [1]. The college years are a stressful period of transition when young adults experience many changes in emotional, social, and identity development – processes that can increase risky behaviors, especially substance use. Use of alcohol, marijuana, and other drugs can contribute to adverse health and social outcomes and threaten students’ ability to successfully obtain a degree, develop enduring social bonds, and participate in the workforce [2–4]; domains of functioning that promote healthy outcomes over the life course [5, 6]. Relatedly, nearly 10% of students report their alcohol use has led to health, social, legal, or financial problems at least once [1]; while over 500,000 students are injured or assaulted, 8.5% are arrested, and approximately 2% attempt suicide every year due to their own or others' substance use [7, 8]. College students and young adults who report past 30-day polysubstance use, such as using both alcohol and marijuana (or other vaping device), or prescription medication (e.g., opioids) in conjunction with alcohol [9], are at especially high risk for major depressive episodes or serious mental illness [10].

Research suggests the negative social, legal, and health-related outcomes linked to substance use may disproportionately affect some populations more than others. While non-Hispanic White young adults report the highest rate of overall alcohol consumption, Hispanic adults are more likely to have higher rates of alcohol dependence, and consume five or more drinks in one sitting than their non-Hispanic White peers [11, 12]. Moreover, the 2006 Hispanic Americans Baseline Alcohol Survey (HABLAS) indicated nearly a quarter of participants reported two or more alcohol-related problems [13]. In regards to opioids, from 2014 to 2017 across all race/ethnic groups, Hispanics had the second highest deaths resulting from synthetic opioids, increasing 617% [14]. In 2019, 5.7% of Hispanics age 18–24 reported misusing opioids or prescription pain meds, 48% reported past month alcohol use, and 20% reported using marijuana in the last 30 days [15]. Such college student data and specifically young adult Hispanic substance use and negative outcomes, underscores the importance of culturally relevant substance use prevention programs on college campuses that can target this at-risk population.

In response to the growing concern of young adult and college student substance use, the National Institute of Alcohol Abuse and Alcoholism (NIAAA) promotes and facilitates the adoption of evidence-based research focusing on individual-level alcohol intervention strategies implemented on college campuses [16], and the Substance Abuse and Mental Health Services Administration (SAMHSA) identifies evidence-based strategies and programs to prevent substance misuse among those 18–25 years old [17]. Current college substance use intervention and prevention programs often utilize traditional face-to-face or online programs to reduce alcohol consumption [16]. Among the highly effective are individual-level strategies, such as brief motivational interventions (BMI) and the Brief Alcohol Screening and Intervention for College Students (BASICS), a face-to-face harm reduction approach incorporating self-management strategies to reduce drinking [18, 19]. Similarly, fully computerized campus E-interventions, especially those that incorporate online alcohol screening and automated personalized feedback, are proving efficacious [20, 21]. AlcoholEdu for College, an online program with knowledge-based quizzes and personalized feedback, positively impacts college alcohol-related attitudes, behaviors, and consequences [22], and has shown short-term effects among freshmen. However, nearly all reported data are from colleges with predominantly non-Hispanic White student bodies [23], and are focused solely on alcohol use. Although face-to-face settings or static web-based methods have proven successful in reducing college alcohol use, in-person settings and current antiquated platforms are limited in scope and versatility, and fail to address polysubstance use among diverse college student bodies.

Currently, only three of the nearly two dozen evidence-based individual-level alcohol and substance use intervention strategies listed by NIAAA are identified as highly effective and low cost: normative re-education, skills training, and personalized feedback (e.g., eCHECKUP TO GO) [20]. Additionally, no programs in SAMHSA’s list of evidence-based programs in college settings to prevent substance misuse among those 18–25 years old include substances beyond alcohol [17]. Some college-based interventions incorporate brief motivational interviewing (e.g., BASICS), that while effective [24, 25], are costlier, targeted toward risky substance users (predominantly alcohol), and generally require face-to-face student interaction [26]. While research has identified several essential ingredients to substance use prevention, few campus prevention efforts have leveraged mHealth delivery systems or web-app technology; and no comprehensive substance use prevention efforts using this medium have been broadly tested [27].

Despite significant progress leading to the identification of modifiable risk and protective factors and effective strategies to prevent substance use and substance use disorders, challenges remain. Evidence-based practices are not being broadly adapted and sustained, and emerging drug trends (e.g., the opioid epidemic, changing policies related to cannabis, vaping/e-cigarettes) present new challenges for prevention research and practice [28–30]. One of the biggest barriers for prevention work with college populations is how to attract and reach student populations. The number of young adults using smart devices to connect with diverse social and didactic networks is increasing [31], as well as their preference for and comfortability with web-based technology. As such, leveraging innovative approaches to rapidly evolving mHealth technology for prevention programming is critical for the success of public health efforts aimed at lowering the risk for substance use and related consequences in college populations, and especially those at Hispanic Serving Institutions.

There is a strong link between Healthy People (HP) 2030’s focus on reducing substance use among young people and the need to develop, test, scale, and sustain evidence-based programs. Especially programs designed to limit engagement in health-compromising behaviors, such as substance use; and prevent progression to risky use in service or educational systems. Importantly, HP 2030 identified the following primary public health objectives: reduce a) the number of adults who use marijuana daily or almost daily, b) the proportion of adults who use drugs in the last month, c) the number of people who misuse prescription drugs and, d) the number of young adults who binge drink; goals this study aims to address [32]. This paper describes the rationale, intervention design, and evaluation of the web-app iSTART (initiative for Services in Tech-Health and Rapid Testing) to prevent substance use (i.e., alcohol, marijuana, nicotine, prescription drugs, and illicit drugs) among college students at a Hispanic Serving Institution. We hypothesize that the intervention will prevent increases, limit, or lower substance use (i.e., measured by baseline, 30-day and 90-day binge drinking, marijuana use, etc.) compared to comparison and control groups. We anticipate that the increases in 1) substance-related knowledge, 2) perceived health risk associated with substance use, 3) confidence in refusal skills, and 4) correcting perceptions of substance use prevalence are the mechanisms that reduce and limit substance use behaviors of students in the prevention condition.

## Methods

### Study design and setting

The design consists of participant recruitment and randomization of participants to either intervention, comparison, or control conditions with a time series evaluation design. The intervention will occur at a large Hispanic Serving public Institution in southern California. The students in the intervention group will receive a 30-day web-app consisting of five substance-specific modules, while the students in the comparison group will receive a single abbreviated module, and those in the control group will only have access to standard online University substance abuse resources. Study data collection periods consist of a baseline survey after recruitment and assignment to condition, an exit survey after completing the 30-day iSTART web-app intervention (or 30-day comparison or control), and a 90-day follow-up survey.

### Study population and recruitment

The study population will consist of college students age 18–30. We will recruit 200 students in the prevention condition, 200 students in the comparison group condition, and 200 students in the matched control condition. We will use mixed models with a random effect for individual to test for the difference in longitudinal slopes with days drinking and marijuana use (example outcomes). We assume an average of 3 measurements per person and a correlation of 0.10 among intra-individual measurements, using a 2-sided test with alpha = 0.05 and 80% power, we will be able to detect a difference in frequency of alcohol and marijuana use at the final endpoint for prevention vs. control and for prevention vs. comparison group with Cohen’s d effect sizes of approximately 0.20 and 0.23, respectively, meaning we will be able to detect small minimum effect sizes among groups. Power analysis indicate that to detect a small effect size, adjusted for covariates across groups (all three groups: control, comparison, and prevention intervention), a minimum of 525 participants are needed over three years. An oversampling of 15% will be conducted to account for possible attrition across surveys. A total sample of 690 college students (evenly randomized to control, comparison, and intervention groups) will be recruited over three years to achieve sufficient statistical power.

Recruitment of student participants will include printed flyers with study information available on campus during tabling events for students at the beginning of the academic term, during campus events (both in-person and virtual) with different campus organizations; posters on lawn signs, campus buildings, and businesses; and electronic posting on digital campus billboards. Students will be invited to participate via email recruitment fliers to Student Housing and through college and department announcements. All recruitment materials will include the intervention website information, where students can review the study requirements, check their eligibility, and enroll in the study. Initial screening of participants includes an electronic review of study objectives, completion of a brief questionnaire for alcohol use disorder (AUD) or substance use disorder (SUD) risk [based on the Diagnostic and Statistical Manual of Mental Disorders, Fifth Edition (DSM-5) criteria], and electronic consent. Exclusion criteria include: individuals who are not college students, under 18 or over 30 years of age, or at high risk for AUD or SUD. Students screened as high risk for AUD or SUD will be referred to additional resources and excluded from the study.

The study adheres to the Belmont Report Ethical Principles and Guidelines for the Protection of Human Subjects of Research. Approval for the intervention study was provided by the Institutional Review Board.

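### The detectable effects of d = 0.20 and 0.23 do not follow from the stated inputs: equal arms give one value for both contrasts, about 0.28 for the final-endpoint difference at 200 per arm

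*Protocol article*

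**What the plan says.** Everything needed stands in the protocol article, Methods, under Study population and recruitment.

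- Arm sizes: "We will recruit 200 students in the prevention condition, 200 students in the comparison group condition, and 200 students in the matched control condition". The same paragraph also gives a larger total, again in equal arms: "A total sample of 690 college students (evenly randomized to control, comparison, and intervention groups"), which is 230 per arm. It also gives a floor: "a minimum of 525 participants are needed over three years", which is 175 per arm.
- Test: a mixed model with a random effect for the individual, testing the difference in longitudinal slopes. Data management and analysis repeats that slopes will be compared between arms.
- Inputs: "We assume an average of 3 measurements per person and a correlation of 0.10 among intra-individual measurements", with two-sided alpha 0.05 and 80% power.
- Claim: "we will be able to detect a difference in frequency of alcohol and marijuana use at the final endpoint", for prevention against control and prevention against comparison, with "effect sizes of approximately 0.20 and 0.23, respectively, meaning we will be able to detect small minimum effect sizes among groups".

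No input is given that differs between the two contrasts.

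**The concern.** Two things look wrong. First, two contrasts that share arm size, number of measurements, correlation, alpha and power are given two different detectable effects. Second, both effects look too small for the quantities named. A correlation of 0.10 makes an average over repeated measurements precise, but it makes a slope or a change score imprecise, because the variance of a slope is proportional to one minus the correlation.

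The claim that small effects are detectable is the article's stated support for its sample size. If the planned test has roughly even odds of detecting d = 0.20, a reader who relies on the printed figure would take a non-significant result as stronger evidence against such an effect than it is.

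**Working it through.** **Inputs.** From Study population and recruitment: n = 200 per arm (230 and 175 as alternatives), 3 measurements, correlation ρ = 0.10, two-sided alpha 0.05, power 80%. From Incentives: the follow-up survey goes out 90 days after the exit survey, so the waves fall at about months 0, 1 and 4. Equal spacing (0, 1, 2) is also tried. The outcome SD is set to 1, since d is standardised. The random-intercept model implies the same correlation ρ between any two waves.

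**Formula.** Detectable d = (1.960 + 0.842) × √(f × 2/n), where f depends on the quantity tested. Power at a given d is Φ(d/SE − 1.960), with SE = √(f × 2/n). At n = 200, 2/n = 0.01.

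**Can the plan's pair be reproduced?** No. Nothing in the formula differs between the two contrasts, so it returns one value for both. This holds for every f and every n.

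**Final-endpoint difference.** f = 1, SE = 0.100, d = 2.802 × 0.100 = 0.280. Adjusting for baseline gives f = 1 − 0.10² = 0.99 and d = 0.279. Unadjusted power at d = 0.20 is Φ(2.00 − 1.96) = 52%; at d = 0.23 it is Φ(2.30 − 1.96) = 63%.

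**Slope difference scaled to the last wave, arm-specific baselines.** f = T²(1 − ρ)/Σ(t − t̄)², where T is the last time.
- Times 0, 1, 2: f = 4 × 0.9/2 = 1.80, SE = 0.134, d = 0.376.
- Times 0, 1, 4: f = 16 × 0.9/8.667 = 1.66, SE = 0.129, d = 0.361.
- Power is 32–34% at d = 0.20 and 40–43% at d = 0.23.

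**Slope difference scaled to the last wave, common baseline.** f = T²(1 − ρ)/[Σt² − ρ(Σt)²/(1 + 2ρ)].
- Times 0, 1, 2: f = 4 × 0.9/(5 − 0.75) = 0.847, d = 0.258.
- Times 0, 1, 4: f = 16 × 0.9/(17 − 2.083) = 0.965, d = 0.275.
- Power at d = 0.20 is 53–58%.

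**Quantities the article does not name, at 200 per arm.**
- Mean of all three waves: f = (1 + 2ρ)/3 = 0.40, d = 0.177.
- Mean of the two post-baseline waves: f = (1 + ρ)/2 = 0.55, d = 0.208.
- Slope per wave (0, 1, 2): 0.376/2 = 0.188.

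**Other arm sizes.**

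| Quantity | 175 per arm | 200 per arm | 230 per arm |
|---|---|---|---|
| Final-endpoint difference | 0.300 | 0.280 | 0.261 |
| Slope to last wave, arm-specific baselines | 0.386–0.402 | 0.361–0.376 | 0.337–0.351 |
| Slope to last wave, common baseline | 0.276–0.294 | 0.258–0.275 | 0.240–0.257 |

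**The case against.** The article does not show its formula, and several nearby quantities do land close to the printed values. At 200 per arm the mean of the two post-baseline waves gives 0.208 and leaves the baseline out. At 175 per arm the per-wave slope gives 0.402/2 = 0.201. At 230 per arm a one-sided final-endpoint test gives 0.232, and prevention against the other two arms pooled gives 0.226. These near misses are real. None of them is the two-sided, pairwise, final-endpoint difference that the article names, and none gives two different values for equal arms. Reading the two values as alcohol and marijuana does not help either, because d is standardised and only one correlation is given.

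A second objection is that the slope figure of 0.36 to 0.38 depends on estimating the baseline separately in each arm, while randomisation makes a common baseline legitimate. That stands, and both models are reported for this reason. Under the kindest combination (230 analysed per arm, common baseline, equal spacing) the detectable d is 0.240, with power 64% at d = 0.20 and 76% at d = 0.23. This still falls short, and it assumes no loss from a number that appears to include the attrition allowance.

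Third, d = 0.28 may itself loosely be called small. That is fair: the firm error lies in the figures 0.20 and 0.23, more than in the adjective.

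**Conclusion.** The point holds. The two values cannot both be right under one set of inputs, whatever the model. Neither is reached by the final-endpoint or slope comparison at 175, 200 or 230 per arm. At 200 per arm the detectable d is about 0.28 at the final endpoint, and 0.36 to 0.38 or 0.26 to 0.275 for the slope, depending on how baseline is handled. These figures assume constant correlation 0.10, a random intercept only, complete data on the stated n and a normal approximation. A random slope or attrition would raise the slope figures; a higher correlation would lower them.

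Four stronger readings are not supported.
- A reader might infer that a time-averaged formula was used. The pattern suggests it, but the article does not say so.
- A reader might take 15% off the 200 per arm. The article oversamples for attrition, and 690 = 600 × 1.15, so 200 can be read as the number left after that allowance.
- A reader might conclude that the minimum of 525 is also miscalculated. The article does not state the model or the covariate strength behind it, so this cannot be shown.
- A reader might conclude that the trial must be enlarged. The error is in a stated figure, and correcting that figure does not require a larger trial.

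**What to change.** Replace the 0.20/0.23 pair with a single detectable d for both pairwise contrasts, computed for the mixed-model slope or final-endpoint test that will actually be used. Beside it, state the model (including whether baseline is common or arm-specific), the time coding, the correlation and the analysed number per arm. For example: about 0.28 for the final-endpoint difference at 200 analysed per arm and correlation 0.10. If the slope is the quantity of interest, give the figure for the chosen baseline handling instead.

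Withdraw the claim of 80% power at d = 0.20 to 0.23 unless a supported higher within-person correlation justifies it. For scale, a slope test with arm-specific baselines at 200 per arm would need a correlation of about 0.72 to 0.75 to reach d = 0.20. An unadjusted final-endpoint comparison gains nothing from a higher correlation.

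The change is to wording only. It needs no extra enrolment and no change to data collection, which is already under way. Its only downside is a less favourable stated figure.

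### The planned sample size is given as both 600 and 690, and 690 does not follow from the stated minimum of 525 plus 15% oversampling

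*Protocol article*

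**What the plan says.** The protocol article gives a sample size in two places.

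- **Abstract, Methods:** the evaluation is described as "using a sample of 600 students randomly assigned to either the intervention, comparison, or control condition".
- **Study population and recruitment, opening:** "We will recruit 200 students in the prevention condition, 200 students in the comparison group condition, and 200 students in the matched control condition". That is 3 × 200 = 600.
- **Same paragraph, power analysis for all three groups:** "a minimum of 525 participants are needed over three years".
- **Same paragraph, allowance:** "An oversampling of 15% will be conducted to account for possible attrition across surveys".
- **Same paragraph, close:** "A total sample of 690 college students (evenly randomized to control, comparison, and intervention groups) will be recruited over three years". That is 690/3 = 230 per arm.

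The detectable effects (Cohen's d of about 0.20 and 0.23) appear between the 200-per-arm sentence and the 525. They are given for "using a 2-sided test with alpha = 0.05 and 80% power", and no sample size is attached to them.

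**The concern.** Both 600 and 690 are called recruited totals, and both are called randomised totals: 600 in the Abstract, 690 at the close of the recruitment paragraph. Nothing says that one replaces the other or that they count students at different stages. The order of the sentences (minimum, then 15%, then total) leads the reader to expect 690 to be 525 plus 15%, and it is not.

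The point at which enrolment ends is therefore ambiguous. The implementation section says the web-app has been launched and that data collection runs for three years, so the target is in use. With both totals published, a trial that closes anywhere from 600 to 690 could be described as on plan. A reader also cannot tell which number, before or after attrition, supports the detectable effects.

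**Working it through.** **Inputs**, all from the protocol article: 600 assigned (Abstract); 200 per arm, minimum 525, oversampling 15%, total 690, and equal allocation (Study population and recruitment).

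**1. Reproduce 690 from the stated minimum.** There are two usual ways to add a 15% allowance:

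- multiplicative oversample: 525 × 1.15 = 603.75, so 604;
- division by the retained fraction: 525/(1 − 0.15) = 617.6, so 618 (206 per arm).

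Neither gives 690, which exceeds them by 86 and 72.

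**2. Find what does give 690.**

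- 600 × 1.15 = 690 exactly.
- 600/0.85 = 705.9, so 706.
- 15% applied twice to 525: 525 × 1.15 × 1.15 = 694.3.

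The exact match is 15% added to the 200-per-arm total. 600 is itself close to 525 plus 15% (604).

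**3. Size of the conflict.** 690 − 600 = 90 students, or 90/600 = 15%. Per arm it is 230 against 200.

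**4. Compare each total with the 525 minimum.** The plan states an oversampling percentage and no attrition rate, so both readings are shown.

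| Randomised | 15% lost (× 0.85) | 15% as multiplicative oversample (/1.15) | Loss at which 525 is just met |
|---|---|---|---|
| 600 | 510 (15 short) | 521.7, about 522 (3 short) | 1 − 525/600 = 12.5% |
| 690 | 586.5, about 586 (61 above) | 600 (75 above) | 1 − 525/690 = 23.9% |

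The two readings imply different losses. A multiplicative 15% oversample covers 1 − 1/1.15 = 13.0%.

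**5. What the shortfall at 600 would cost.** Assume that 525 gives 80% power for a two-sided 5% comparison on one degree of freedom. Then 510 gives (1.960 + 0.842) × √(510/525) − 1.960 = 2.802 × 0.9856 − 1.960 = 0.80, which corresponds to about 79% power.

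**6. Effect of 690 on the detectable effects.** Assume these were computed on 200 per arm. With 230 randomised per arm and 15% lost, 230 × 0.85 = 195.5 remain. The detectable d scales by √(200/195.5) = 1.011, so 0.20 becomes 0.202 and 0.23 becomes 0.233. If the 15% is a multiplicative oversample, 230/1.15 = 200 and nothing changes.

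**Not checked.** The 525 cannot be reproduced, because the effect is called only small and the covariates are not listed. Nothing above depends on whether 525 is right.

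**The case against.** The strongest defence is that the figures form a sensible chain: 525 is a floor, 200 per arm (600) is the working target for students with data, and 15% is added to reach 690. The arithmetic of 600 × 1.15 is exact, and the closing sentence names 690 as the number that secures power. This may well be what was intended. It does not fit the wording, because the recruitment paragraph says the 600 are recruited and the Abstract says they are randomly assigned. It also leaves the 525 without a role in the derivation. Treating 690 as enrolled and 600 as reaching randomisation at first login fails too, since the 690 are described as "evenly randomized to control, comparison, and intervention groups" and the allowance is for losses across surveys.

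Other parts of the defence stand, and they rule out stronger readings that a reader might infer:

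- **That the trial falls below its own minimum.** This needs enrolment to stop at 600. The closing sentence says 690, where the minimum is met comfortably.
- **That the plan assumes 15% attrition and inflated for it wrongly.** The text states an oversample for possible attrition and gives no rate. Multiplying by 1.15 is a legitimate reading, so 510 is an assumption about loss and not the plan's own figure.
- **That a student lost at one survey is lost to the analysis.** The planned mixed models with a random effect for individual can use partial follow-up, so even the 510 is pessimistic.
- **That the power statement is wrong at 690.** It names no sample size, and step 6 shows a change of about 1%.
- **That the 15% was counted twice.** The numbers suggest it, but the document never derives 600 from 525.

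**Conclusion.** The inconsistency holds. The document gives two incompatible totals, 600 and 690, which differ by 90 students (15% of 600) between the Abstract and the recruitment paragraph and within that paragraph. The stated route to 690 does not reproduce: 525 plus 15% is 604 or 618. This follows from the text and needs no outside assumption.

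The consequence for power is small and conditional. At 690 the minimum is safe for losses up to 23.9%. At 600 it would be missed by 15 students if 15% contribute nothing, or by 3 if the 15% is a multiplicative oversample; in the first case power would be about 79% instead of 80%, given that 525 delivers 80%. The documents support neither the conclusion that the trial is underpowered nor the conclusion that its detectable effects are wrong. What needs correcting is the stated target itself: as written, it does not tell a reader when enrolment is complete or which number the power claim rests on.

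**What to change.** State one randomised total and use it in the Abstract, the per-arm numbers and the power paragraph. Show how it was derived, and say whether 600 is before or after attrition.

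- **If 690 is the target:** write 230 randomised per arm, replace 600 and 200 per arm where they are described as recruited or assigned, and give the expected evaluable number as about 195 to 200 per arm (230 × 0.85 to 230/1.15). Derive 690 from 600, and explain how 600 relates to the minimum of 525.
- **If 525 evaluable is the requirement:** write 604 randomised (525 × 1.15; equal arms need 202 each, 606) or 618 (525/0.85; 206 each), and say which meaning of 15% is used.

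In either case, name the number per arm behind the detectable effects of 0.20 and 0.23 and say whether it is before or after attrition.

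The cost is a few sentences of wording. The design and analysis do not change, and no enrolment beyond the stated 690 is needed. It should be settled before recruitment closes, so that the target is not chosen in the light of the number achieved.
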